### Focus groups

Knowledge translation activities require an in-depth understanding of the context of the user-groups such as: In what formal or informal structures is the user group embedded? What is the political climate surrounding the user group? To whom is the user group accountable? Are changes expected in any of these? [26]. Therefore, focus group interviews of nursing and medical staff will be used to examine these socio-cultural mediating factors that may influence calling for help using the MET system. A minimum of ten focus group interviews will be taken from representative individuals from the four hospitals using criterion and maximum variation sampling [15]. Participants will be sampled by profession (nursing and medicine) and institution (hospital), and stratified by level of experience within the nursing and medical professions and by institutional location. The participants own experience of the MET call system along with aspects of professional, local, and organisational culture will be sought.

After transcription, themes will be identified from both the focus groups and interviews of barriers to calling of the MET. The Agency for Healthcare Research and Quality (AHRQ) Hospital Survey on Patient Safety Culture (HSOPSC) [27] will be completed by all the clinical staff on the pilot wards before and at three months after the interventions have been introduced. Differences between the responses before and after the intervention on the pilot wards will be analysed using a one-way repeated measures ANOVA.

### Prospective audit

Analysis of all unplanned ICU admissions and cardiac arrests will be performed over an eight-week period before the intervention and an eight-week period three months following implementation of the interventions across all four hospitals in the study.

The clinical notes of all unplanned ICU admissions and cardiac arrests will be examined for evidence of a 'missed MET' in the preceding hours or days. This will determine if an early intervention may have prevented the patient becoming critically ill. Clinical staff involved in the care of a patient that has a 'missed MET' will be interviewed using the same structured interview used in the point prevalence study.

The prospective audit will further allow the barriers to the MET call to be determined from actual cases. Furthermore, the incidence of 'missed MET' will be able to be determined.

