### Redesigning the MET system

In any knowledge translation activity, it is essential that the end users of the knowledge are included to ensure that the knowledge and its subsequent implementation are relevant to their needs [25]. Once the scope and barriers to the RRS are understood, we will pilot a redesign of the RRS to increase its effectiveness. Evaluation of these interventions will be determined by repeat measurements from the first two phases of the study (Figure 2).

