## Methods

Three related studies will be undertaken concurrently with data collected before and after the design and implementation of an intervention to address the issues identified (Figure 2).

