### Point prevalence study

The prevalence of patients meeting the physiological criteria for MET calls will be measured across four hospitals of differing size and caseload over a 24-hour period. These hospitals include an outer suburban 520 bed acute hospital, a small 120 bed elective surgical and oncology centre, a large metropolitan teaching hospital, and an outer suburban community hospital. These four hospitals comprise the majority of the acute care of a health network with over 12,000 staff, 2,100 beds and 180,000 hospital admissions. A team of researchers will examine the clinical notes of all adult in-patients that are not being cared for in critical care areas (ICU, emergency department, or operating theatres). The clinical staff involved with those patients at the time the criteria were attained will be interviewed to determine why a MET call had not been made. Data collected from these structured interviews will be used due to the time constraints of the study and potential to interrupt clinical work. The interview questions will be based on the theoretical framework given in Figure 1. All of the patients identified will be followed up to discharge from hospital to determine if the rate of adverse outcomes in patients meeting the physiological criteria. Particular note will be made to determine if any of these patients subsequently became critically ill, require ICU admission or a cardiac arrest call.

This point prevalence study will be the main study determining the scope of the problem, and to define the 'missed MET' for future study. The data collected from the interviews are expected to be sketchy in terms of determining barriers to the MET call due to the limited time available, but may inform the direction of later phases.

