### Intervention design

Adapting knowledge to the local context is a crucial component in the knowledge translation process [25]. Up to six common barriers identified from the point prevalence, focus group, interview, and prospective case methods will be determined. These barriers will be presented at a workshop consisting of up to twenty clinical staff involved in the MET call process. Case studies will be used to illustrate how the barriers contribute to 'missed MET' calls, and the participants in the workshop will be asked to provide solutions. The potential solutions will then be categorised using the Human Factors Analysis and Classification System (HFACS), and solutions developed using the Human Factors Intervention Matrix (HFIX) [28]. These potential solutions will be rated in terms of feasibility, acceptability, cost effectiveness, effectiveness, and sustainability. Up to five solutions will be chosen, and be implemented as part of the redesign process. The effects of each individual intervention will not be assessed separately.

Six clinical areas will be chosen from the four hospital sites to introduce the redesigned MET system. These six areas will also have additional point prevalence surveys to determine if the mechanism for dealing with the physiologically unstable patient has changed after introduction of the new system. A further prospective audit will also be used to assess the effectiveness of the redesigned solution.

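### The redesign reaches six clinical areas but is judged by a four-hospital before/after audit that gives the unexposed wards no comparison role, so background change cannot be separated from a redesign effect

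*Protocol article*

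**What the plan says.** The Methods section of the Protocol article sets a before/after design: "Three related studies will be undertaken concurrently with data collected before and after the design and implementation of an intervention". Under Redesigning the MET system, the basis for judging the redesign is given as: "Evaluation of these interventions will be determined by repeat measurements from the first two phases of the study".

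The exposure is limited. Intervention design says: "Six clinical areas will be chosen from the four hospital sites to introduce the redesigned MET system". The measurements differ in coverage:

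- **Audit.** The Prospective audit section says: "Analysis of all unplanned ICU admissions and cardiac arrests will be performed over an eight-week period before the intervention". A second window of the same length follows three months after implementation, and both windows cover all four hospitals. Intervention design gives the repeat audit its purpose: "A further prospective audit will also be used to assess the effectiveness of the redesigned solution".
- **Point prevalence.** The baseline survey covers adult in-patients outside critical care and "will be measured across four hospitals of differing size and caseload over a 24-hour period". The repeat is stated for the pilot areas only: "These six areas will also have additional point prevalence surveys to determine if the mechanism for dealing with the physiologically unstable patient has changed".
- **Safety-culture survey.** Under Focus groups, this is completed on the pilot wards before and three months after, and analysed by one-way repeated measures ANOVA.

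The article names no comparison wards, calendar matching, repeated time points or trend adjustment. The Discussion does not list season or secular change as a limitation.

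**The concern.** With one window on each side, the estimate is the redesign effect plus whatever else changed in between: season, casemix, staffing, other hospital initiatives, or the effect of auditing staff and interviewing them about missed calls. Two windows cannot split these parts.

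The audit also spans all four hospitals while only six areas receive the redesign. No split by exposure is stated, so the comparison as written mixes a minority of exposed wards with many unexposed ones. A real benefit is shrunk towards no effect, while background change acts at full size.

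The third aim, improving the effectiveness of the rapid response system, is at stake. The aims on scope and on barriers do not depend on this comparison.

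**Working it through.** The article gives no event rate, effect size, power or test for the audit, so there is no figure to reproduce. Apart from the window lengths, the inputs below are assumptions, shown over ranges.

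**1. Offset between windows.** Take three months as 13 weeks and let G be the unstated design and implementation time. The start-to-start gap is 8 + G + 13 weeks, so at least 21 weeks. The barriers found in the audit feed the design workshop, so G exceeds zero. The windows share a season only if G is about 31 weeks (8 + 31 + 13 = 52), which the article does not arrange.

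**2. Season alone.** Take a yearly sinusoid of amplitude a. Averaging over 8 weeks multiplies a by sin(8π/52)/(8π/52) = 0.96. A 21-week gap gives a largest swing of ±a × 0.96 × sin(21π/52) = ±0.918a about the mean. The extreme ratios with no redesign effect are (1 − 0.918a)/(1 + 0.918a) and its inverse:

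| a | Lowest ratio | Highest ratio |
|---|---|---|
| 5% | 0.91 | 1.10 |
| 10% | 0.83 | 1.20 |
| 15% | 0.76 | 1.32 |

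**3. If the change in counts were tested.** Let E be the baseline events, r the background rate ratio, and the redesign effect zero. Then SE = √(1/E + 1/(Er)), and a two-sided 5% test rejects with probability Φ(−1.96 − m) + Φ(−1.96 + m), where m = ln(r)/SE. For E = 200 and r = 0.85, SE = √(1/200 + 1/170) = 0.104 and m = −0.1625/0.104 = −1.56, so the probability is about Φ(−0.40) = 0.34.

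| E | r = 0.95 | r = 0.90 | r = 0.85 | r = 0.80 |
|---|---|---|---|---|
| 50 | 6% | 8% | 12% | 18% |
| 100 | 7% | 11% | 20% | 32% |
| 200 | 8% | 18% | 34% | 56% |
| 400 | 11% | 31% | 60% | 85% |

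**4. Dilution.** If the pilot areas supply a share p of events and their rate falls by one-third, the overall rate ratio is 1 − p/3. This is 0.97, 0.93 and 0.90 for p = 10%, 20% and 30%. The one-third is borrowed, for illustration only, from the Abstract's figure for introducing a rapid response team. All three values lie inside the 10% seasonal range in step 2.

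**5. Concurrent contrast.** Divide the pilot areas' before/after rate ratio by that of the non-pilot wards. Drift common to both cancels and the expected ratio is 1 when the redesign does nothing. The 95% interval is the estimate times or divided by exp(1.96 × √(1/(pE) + 1/(pEr) + 1/((1−p)E) + 1/((1−p)Er))). For E = 200, p = 0.1 and r = 0.85 the expected counts are 20, 17, 180 and 153. The root is √(0.0500 + 0.0588 + 0.0056 + 0.0065) = 0.348, and exp(0.682) = 1.98.

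| E | p = 10% | p = 20% | p = 30% |
|---|---|---|---|
| 200 | 1.98 | 1.67 | 1.56 |
| 400 | 1.62 | 1.44 | 1.37 |

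These factors use Poisson variation only. Clustering by ward would usually widen them.

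**The case against.** The strongest reply has four parts.

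- **It is a pilot.** The article calls the redesign a pilot, and an uncontrolled evaluation can be reasonable there if labelled as such. This limits the weight of the point but does not remove it, because the repeat audit is assigned to assessing effectiveness.
- **The analysis may be fixed elsewhere.** Both audit windows cover all four hospitals, so a fuller plan could still use the non-pilot wards. This stands as regards the model. The basis of evaluation is not left open, however: the article fixes it as repeated measurement and names no comparator.
- **No test on counts is stated.** The audit's explicit outputs are barriers and the incidence of missed METs. If that incidence is expressed per audited event, a seasonal change in volume alone need not move it. This stands, so the rejection probabilities are illustrations. A general change in calling behaviour would still move the proportion.
- **The concurrent contrast is imprecise.** With a factor above 1.5, an estimate of exactly two-thirds would not exclude no effect. That applies to every 200-event case shown and to 400 events at a 10% share. The four-hospital comparison is no rescue. At 200 baseline events and an overall ratio of 0.90, SE = √(1/200 + 1/180) = 0.103, giving an interval of about 0.74 to 1.10 around a diluted and confounded quantity.

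A reader might also infer more than the article supports. No dates are given, so different seasons are a possibility and not a stated fact. Nothing sets the hospital-wide baseline prevalence against follow-up in the six areas. The baseline should already include their in-patients, and a repeat in those areas to see whether practice changed most naturally means the same areas twice. Regression to the mean would arise only if areas were picked for poor baseline results, and no selection rule is given.

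**Conclusion.** The point holds in this form: the effectiveness evaluation has no stated comparator and no calendar matching, so background change cannot be separated from a redesign effect, and the four-hospital audit dilutes whatever effect exists. The document fixes the six exposed areas, the four-hospital audit and a gap of at least 21 weeks.

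The sizes rest on assumptions. A pilot share of 10–30% turns a one-third reduction into an overall ratio of 0.97–0.90. A 10% seasonal amplitude alone could give 0.83–1.20. It does not follow that drift will be declared an effect, since no test is named for the audit. The data as described simply could not tell the two apart.

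**What to change.** - Record the ward of origin for every audited event in both windows.
- Define the effectiveness contrast as the change in the six pilot areas minus the concurrent change in the non-pilot wards, on the log-rate scale for event counts, using a ward-type by period term and allowing for clustering by ward. Apply the same contrast to missed METs.
- State that point prevalence is compared within the same six areas at baseline and follow-up.
- Where the schedule allows, place the two audit windows in the same calendar weeks. This addresses season but not secular trend.
- Report any before/after result without a comparator, including the pilot-ward survey, as descriptive.

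Surveying some non-pilot areas at follow-up is optional and needs extra staff time. Choosing the six areas without reference to baseline results would remove the conditional risk of regression to the mean.

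The audit contrast needs no new event collection beyond ward of origin. Its price is precision: on 200–400 assumed baseline events, the 95% interval is the estimate times or divided by about 1.4–2.0. Spill-over within hospitals could pull the contrast towards zero. The pilot areas are chosen, not randomised, so change specific to them would remain a limitation.

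### The redesign goes into six clinical areas, but the audit also used to assess it is specified across four hospitals, so a local effect is diluted by the areas' unstated share of events

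*Protocol article*

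**What the plan says.** The protocol article gives the redesign a narrow footprint. Under Intervention design: "Six clinical areas will be chosen from the four hospital sites to introduce the redesigned MET system". The same paragraph gives the audit an evaluative role: "A further prospective audit will also be used to assess the effectiveness of the redesigned solution".

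The audit's scope is set under Prospective audit. The baseline part reads "Analysis of all unplanned ICU admissions and cardiac arrests will be performed over an eight-week period before the intervention", and the follow-up part is "an eight-week period three months following implementation of the interventions across all four hospitals in the study".

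The other two before/after measures follow the redesign's footprint. On the repeat prevalence work, Intervention design says "These six areas will also have additional point prevalence surveys to determine if the mechanism for dealing with the physiologically unstable patient has changed". The safety culture survey, described under Focus groups, "will be completed by all the clinical staff on the pilot wards before and at three months after the interventions have been introduced".

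The article gives no size for the six areas, no expected number of audited events and no target effect.

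**The concern.** Of the three before/after measures, the audit is the one that counts unplanned ICU admissions and cardiac arrests, the outcomes that the Discussion hopes to reduce. It is also the only one whose stated coverage is wider than the area receiving the redesign. If the two eight-week windows are compared over the four hospitals, most of the events counted probably come from wards where the redesign was not introduced.

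Two misreadings could follow. A redesign that works locally could look ineffective. A hospital-wide change unrelated to the redesign could be credited to it, because no non-pilot comparison is stated.

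**Working it through.** The article has no sample size, power or event figure to reproduce. The check is therefore how much a local effect shrinks under the stated scope.

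**Inputs from the article.** Six areas; four hospitals; two of these hold 520 + 120 = 640 beds ("These hospitals include an outer suburban 520 bed acute hospital, a small 120 bed elective surgical and oncology centre"); the other two are unsized. The network total is 2,100 beds ("a health network with over 12,000 staff, 2,100 beds and 180,000 hospital admissions"), which caps the four-hospital total.

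**Assumptions not in the article.** 20 to 40 beds per area; 1,000 to 2,100 beds in the four hospitals; event rate in the pilot areas k = 1 or 2 times that of other wards; local reduction e of one-half or one-third; no spill-over; 100 to 800 audited events per window.

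**Step 1: share of events.** With bed share b = 6 × (beds per area) / (four-hospital beds), the event share is w = kb / (1 − b + kb). For example, b = 6 × 40 / 1,000 = 0.24 and k = 2 give w = 0.48 / 1.24 = 0.387.

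**Step 2: dilution.** The overall reduction is w × e.

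| Beds per area | Four-hospital beds | k | w | Halving appears as | One-third reduction appears as |
|---|---|---|---|---|---|
| 20 | 2,100 | 1 | 5.7% | 2.9% | 1.9% |
| 30 | 1,500 | 1 | 12.0% | 6.0% | 4.0% |
| 40 | 1,000 | 1 | 24.0% | 12.0% | 8.0% |
| 20 | 2,100 | 2 | 10.8% | 5.4% | 3.6% |
| 40 | 1,000 | 2 | 38.7% | 19.4% | 12.9% |

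**Step 3: what this does to a comparison of counts.** For two Poisson counts m1 and m2 with equal exposure, approximate power at two-sided 5% is Φ(|ln(m2/m1)| / √(1/m1 + 1/m2) − 1.96).

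Take 200 baseline events, w = 0.12 and a halving in the pilot areas:

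- Four hospitals: 200 against 200 × 0.94 = 188. |ln 0.94| = 0.0619 and SE = √(1/200 + 1/188) = 0.1016, so the ratio is 0.61 and power is about 9%.
- Six areas: 24 against 12. ln 2 = 0.693 and SE = √(1/24 + 1/12) = 0.354, so the ratio is 1.96 and power is about 50%.

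At the same 200 events and the same halving, other shares give:

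| w | Power, four hospitals | Power, six areas |
|---|---|---|
| 6% | 5% | 28% |
| 12% | 9% | 50% |
| 24% | 24% | 79% |
| 40% | 56% | 95% |

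Over 100 to 800 events and shares of 6% to 40%, the six-area contrast has the higher power for a halving in every case run. The size of the gap depends on the inputs; its direction does not. At the favourable end the pooled comparison is respectable: with w = 40%, power is 85% at 400 events and 99% at 800.

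**Step 4: limit of the remedy.** For 80% power, the six areas would need about 50 baseline events to detect a halving, or about 120 to detect a one-third reduction. In the example above they have 24, and the 95% interval for the rate ratio, exp(−0.693 ± 1.96 × 0.354), runs from 0.25 to 1.00.

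**The case against.** The strongest reply is that the Prospective audit section fixes where and when cases are collected, not how the two windows are compared. It writes no pooled test and no denominator, and it does not name total event counts as the measure of effect. Notes are reviewed case by case, so an analysis by ward looks feasible and may sit in a fuller document that is not shown. A reader might also take the further audit to be confined to the six areas, since it is mentioned directly after them. This stands as far as it goes: four-hospital collection does not rule out a pilot-area analysis. But the only scope stated for the audit is all four hospitals, and the article confines its other two before/after measures where it wants to.

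The audit also has purposes for which wide coverage is right: finding barriers from actual cases and measuring the incidence of missed MET calls. That stands fully, and collection should not be narrowed. The audit is not the sole evaluation either, since two matched measures exist.

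Zero spill-over is an assumption. The Discussion allows for solutions such as policy or education that could reach other wards. Spill-over would lessen the dilution and would also make the other wards an imperfect comparison.

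A reader might go further and infer that even a large effect shrinks to almost nothing, or that the audit cannot inform on the redesign at all. The documents do not support either reading. The share of events is not given, a halving could still show as 12% to 19% overall, and the case-level data could be analysed by area.

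**Conclusion.** The mismatch between where the redesign is introduced and where the audit counts events is in the text and should be corrected. Without spill-over, the overall effect equals the local effect times the six areas' share of events. For a halving, that is a fall of about 3% to 12% at equal event rates, and about 5% to 19% if pilot areas have double the rate of other wards.

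These ranges rest on assumed bed numbers and relative event rates, and the power figures additionally on assumed event counts; all are illustrative. What does not rest on them is that a pooled figure understates a purely local effect whenever the share is below one. The evaluation as a whole is not invalid, because the prevalence and safety culture measures already match the pilot areas.

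**What to change.** - Keep four-hospital collection for the barrier and missed-MET incidence aims.
- Record the ward of origin for every audited event in both windows.
- State that the effectiveness contrast is the before/after change in the six pilot areas, per admissions or bed-days of those areas.
- Report the remaining wards separately as a concurrent non-pilot comparison, and note that spill-over may have reached them.
- Do not judge the redesign on the pooled four-hospital figure.
- State the number of events expected in the six areas and report the estimate with its interval.

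The cost is one extra field in an audit that already reads the notes, denominators for the six areas and the other wards, and a few sentences of analysis wording. The downside is precision: few events will fall in six areas over eight weeks, so the interval will be wide and a non-significant result must not be read as no effect.
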